### Measurements

#### Main outcome

The study main outcome is the TC’s self-reported stress as measured by the Calgary Symptoms of Stress Inventory (C-SOSI), a validated 56-item scale designed to assess various subjective symptoms of stress with 8 factor derived subscales, each consisting of 6-9 items: Depression, Anger, Muscle Tension, Cardiopulmonary Arousal, Sympathetic Arousal, Neurological/GI, Cognitive Disorganization, and Upper Respiratory Symptoms [57]. Subjects are asked to indicate the frequency with which they have experienced a particular symptom during the prior one week timeframe.

#### Mediating variables

Data regarding the following variables hypothesized to serve as mediators to the main outcome will be collected.*Social Support***:** Perceptions regarding social support (at work with coworkers and at home with family and friends), assessed by two separate visual analogue scales (VAS). Prior research has established the reliability and concurrent validity of these measures in another first responder sample [58].*Network Conflict*: The degree of conflict experienced at home and at work, assessed by two separate VAS. Prior research has established the reliability and concurrent validity of these measures in another first responder sample [58].*Mindfulness*: The Mindful Attention Awareness Scale (MAAS) will assess attentional sensitivity to psychological, somatic, and environmental cues [59]. Prior research has documented internal consistency reliability estimates were of good quality (α ranged = .89–.93) and test–retest reliability correlations between the repeated MAAS measures were all of medium-to-large magnitude and statistically significant [60]. The Five Facet Mindfulness Questionnaire (FFMQ) will assess five factors associated with mindfulness. Sound psychometric properties for the FFMQ have been consistently observed, including construct validity for the global FFMQ score, as well as adequate to strong internal consistency for the global score and subscales (α = .67-.93) [61–68]. The five factor hierarchical structure has been confirmed in samples of mediators and non-mediators [61, 68].

#### Covariates

We will collect the following data that may serve as covariates or confounders with our main outcome.*Demographics*: Participants are asked to provide their age, gender, and years of experience as 9-1-1 TCs.*Overcommitment (OC)*: OC refers to an individual’s exhaustive coping style which can adversely impact the health and well-being. [69, 70]. In our prior work, OC has been positively related to symptoms of stress and negatively related to mindfulness in a sample of 9-1-1 TCs [39]. OC items are drawn from the Effort-Reward Imbalance (ERI) scale used to measure occupational efforts relative to rewards [69]. We will add one item to increase its relevance to 9-1-1 TC work.*Overtime*: 9-1-1 TCs will be asked if they have worked overtime, and if it was voluntary or mandatory.*Acute stressor or stress event*: Call center managers will be asked if there was an unusual organization-wide acute stressful event during the study period.*Job Demands - mental*: Measured with the Mental Demands subscale (5 items) from the National Institutes for Occupational Safety and Health (NIOSH) Generic Job Stress Questionnaire. [71, 72]*Job Demands - physical*: Measured with the Job Requirements subscale (10 items) from the NIOSH Generic Job Stress Questionnaire. [71, 73]*Technostress*: Technostress is measured using items drawn from the Techno-uncertainty and Techno-insecurity sub-scales of the Technostress creators’ Scale [74] and we will add one Techno-insecurity item specific to 9-1-1 TC work.

### Sample size and power calculations

We anticipate randomizing a total of 160 9-1-1 TCs into two groups (~ 80 per group), and obtaining outcome data on survey measures from a minimum of 65 per group after accounting for attrition (allowing for a loss to follow-up of about 20%). A rough estimate of a clinically meaningful effect size was obtained after review of studies of mindfulness interventions that used the C-SOSI or SOSI measure as an outcome. We found seven studies [75–81] that reported sufficient information to estimate the effect size and within-participant standard deviations. These suggest that an effect size of 0.4 to 0.5 represents a clinically meaningful effect size. Based on our prior work measuring 9-1-1 TC stress utilizing the C-SOSI, this corresponds to a change in C-SOSI score of about 15 [39]. To give some context, in an unpublished analysis of stress in this population, a change in C-SOSI score of 15 was associated with a 30% increase in the use of sick days. Power calculations were performed using a two-sample t-test of the pre-post difference in C-SOSI scores, under the assumption of an effect size of 0.5, a type I error rate of 5%. To achieve 80% power requires data on 65 participants per group; allowing for a loss to follow up rate of 18% would require a total of 160 participants.

### Statistical analyses

The primary hypothesis for this intervention study is that TCs who are randomized to the online mindfulness training will report fewer symptoms of stress compared to TCs who are randomized to the wait-listed control group.

#### Primary analyses

To examine the primary hypothesis we will use repeated measures mixed effects models, with differences assessed by interaction terms between randomization group and follow-up time. The models will include fixed effects for group (2 levels) and time (3 levels; baseline, post intervention and follow up), site, time–by-treatment interaction, and an interaction term between the implementation of the center wide toolkit and the third time point, with a random intercept for participant. Differences between groups will be assessed using the time-by-treatment interaction term.

The primary outcome variable will be the C-SOSI symptoms of stress scale. Hypotheses will be conducted at the 0.05 level of significance without adjustment for multiple comparisons, with group assigned according to intent-to-treat.

The effects of possible differential drop-out rates between the two groups will be assessed using sensitivity analyses under the assumption that data is not missing at random. Multiple imputation will be used to impute missing values for the outcome variable under varying levels of bias, and the resulting association between level of bias and differences between the groups estimated.

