### Randomization

Respondents from each enrolled call center who are eligible, have provided their informed consent, and have completed the baseline survey, will be randomized into either the mindfulness training group or wait-list control group.

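### The primary model estimates a baseline group difference that randomization already sets to zero, which costs precision (not validity) on the C-SOSI contrast

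*Protocol article*

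**What the plan says.** Under Primary analyses, the protocol article specifies a repeated-measures mixed model: "The models will include fixed effects for group (2 levels) and time (3 levels; baseline, post intervention and follow up), site". The model also has a time-by-treatment interaction, a toolkit term at the third time point and a random intercept for participant. Group differences are judged by the time-by-treatment interaction. Neither a baseline covariate nor a shared baseline mean is mentioned.

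Under Randomization, those who are eligible, have consented and "have completed the baseline survey, will be randomized into either the mindfulness training group or wait-list control group". Baseline is therefore measured before allocation.

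Under Sample size and power calculations, the trial is sized on the same kind of contrast: "Power calculations were performed using a two-sample t-test of the pre-post difference in C-SOSI scores". The meaningful range is wider than the value used for power: "These suggest that an effect size of 0.4 to 0.5 represents a clinically meaningful effect size".

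Under Secondary analyses, the same model is reused for MAAS and for the four visual analogue scales.

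**The concern.** When baseline is an outcome time and group has a free main effect, the model fits a separate baseline mean for each arm. The interaction at survey 2 is then the group difference at survey 2 minus the group difference at baseline. Because allocation follows the baseline survey, the second quantity is zero in expectation. What is subtracted is sampling noise, and a chance imbalance at baseline is removed one-for-one rather than in proportion to how well baseline predicts follow-up.

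Precision on the primary contrast is at stake. The trial is powered at 0.5, the top of its own meaningful range, so at 0.4 there is little to spare. The same model serves five secondary outcomes, so the loss recurs there.

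**Working it through.** **Inputs from the article.** The power calculation is made "under the assumption of an effect size of 0.5, a type I error rate of 5" per cent. Evaluable numbers: "To achieve 80% power requires data on 65 participants per group". Allocation: "randomizing a total of 160 9-1-1 TCs into two groups (~ 80 per group". Raw difference: "this corresponds to a change in C-SOSI score of about 15" points, which implies an SD of 15/0.5 = 30 or 15/0.4 = 37.5. The article does not say whether that is the SD of the score or of the change.

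**Assumptions.** The test is two-sided. C-SOSI has equal variance s² at each survey. The correlation is the same, r, between any two surveys (this is what a random intercept implies). r is not given, so a range is shown. Site and toolkit terms are left out of the calculation.

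**1. The plan's own figure.** A two-sample t-test at effect size 0.5 and 80% power needs 64 per group (63 by the normal approximation), against 65 stated. Power at 65 per group is 81%. Allowing for 18% loss, 130/0.82 rounds up to 159, against 160 stated. The sample size reproduces. At effect size 0.4 the same test has 62% power.

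**2. Complete data, n = 65 per arm, survey-2 contrast.**
- Free group effect (difference in change): 4s²(1−r)/n.
- Common baseline mean: 2s²(1−r²)/n.
- Ratio: (1+r)/2, so the variance falls by (1−r)/2.

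That is 25% at r = 0.5, 15% at 0.7 and 10% at 0.8.

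**3. Planned attrition, 80 per arm at baseline and 65 followed.** The planned mixed model already draws some information from the 15 per arm who have a baseline only.
- Free group effect: 2s²(1−r²)/65 + 2s²(1−r)²/80.
- Common baseline mean: 2s²(1−r²)/65.

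In units of s²:

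| r | Free | Common baseline | Fall |
|---|---|---|---|
| 0.3 | 0.02800 + 0.01225 = 0.04025 | 0.02800 | 30% |
| 0.5 | 0.02308 + 0.00625 = 0.02933 | 0.02308 | 21% |
| 0.7 | 0.01569 + 0.00225 = 0.01794 | 0.01569 | 12.5% |
| 0.8 | 0.01108 + 0.00100 = 0.01208 | 0.01108 | 8% |
| 0.9 | 0.00585 + 0.00025 = 0.00610 | 0.00585 | 4% |

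A generalized least squares calculation for two groups and three times gives the same values.

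**4. Power with attrition, effect size d on the SD of change.** This is what a t-test on change scores implies. The effective d is d × √[(4s²(1−r)/65) / V], where V is the variance from step 3, and it is entered in the t-test with 65 per arm. For example, at r = 0.5 and d = 0.5 the free model gives 0.5 × √(0.03077/0.02933) = 0.512, and the common-baseline model gives 0.5 × √(0.03077/0.02308) = 0.577.

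| d | r | Planned model | Common baseline |
|---|---|---|---|
| 0.5 | 0.5 / 0.7 / 0.8 | 83% / 82% / 82% | 90% / 87% / 85% |
| 0.4 | 0.5 / 0.7 / 0.8 | 64% / 63% / 63% | 74% / 69% / 66% |

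**5. Effect size on the SD of the score instead.** The SD of change is s√[2(1−r)], so the two readings coincide at r = 0.5. With complete data and d = 0.5, power of the change contrast is 96% at r = 0.7 and 99% at r = 0.8. The common-baseline model gives 98% and over 99%, so little is left to gain. At r = 0.3 the figures are 67% and 84%.

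**The case against.** The strongest reply is that nothing here is invalid. A three-time mixed model with group, time and their interaction is a standard analysis. It gives an unbiased contrast with the correct type I error, and it matches the change-score t-test used for the sample size. All of that stands, and it makes this point an improvement rather than the correction of an error.

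A reader might infer that chance imbalance or regression to the mean distorts the result. The documents do not support that. Under randomization, regression to the mean is expected equally in both arms and cancels in the difference in change. Only variance remains.

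A reader might also take a 10–25% variance saving as a property of this trial. It is not. It needs r between 0.5 and 0.8 and complete data, and the article plans for attrition and gives no r. The power gains also depend on which SD the effect size refers to.

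Finally, the common-baseline model takes its weight on baseline from the covariance structure, so a random intercept alone makes it rely on equal variances and correlations over time. That is fair. It limits how exact the figures above are, but it does not remove the reason for the change.

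**Conclusion.** The point holds as one of efficiency. The planned primary contrast is less precise than the design allows for any r below 1, under equal variances and the stated random intercept. With the planned attrition, the avoidable share of the survey-2 variance is about 21%, 12.5% or 8% at r = 0.5, 0.7 or 0.8, and runs from about 30% to 4% over r = 0.3 to 0.9.

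On the SD-of-change reading, the stated 80% power at effect size 0.5 is met without any change. The gain is about 3 to 8 points at 0.5 and about 4 to 10 points at 0.4 for r between 0.8 and 0.5. On the SD-of-score reading the gain is smaller at r = 0.7 or above. It would be wrong to conclude that the trial is mis-sized or its primary test faulty. The change is worth making because the baseline is already collected and power at 0.4, which the article itself calls meaningful, is otherwise only about 63%.

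**What to change.** Drop the group main effect so that both arms share one baseline mean (a constrained longitudinal model). Keep separate group-by-survey-2 and group-by-survey-3 terms, coded as explicit indicators so that the software does not put a baseline group difference back in. State whether the random intercept is kept as the only covariance structure; an unstructured covariance over the three surveys would avoid relying on equal variances and correlations. Apply the same mean structure to MAAS and the four VAS outcomes, and state the assumed r and which SD the effect size refers to.

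A close alternative uses surveys 2 and 3 as outcomes, with baseline C-SOSI and its interaction with time as covariates. It drops participants who have only a baseline (about 15 of 80 per arm on the plan's figures). The constrained model keeps everyone randomized, since completing the baseline survey is a condition of entry.

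The cost is one model term, set before analysis. No new data or recruits are needed.

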### Description, Design & Development of Interventions

#### Individual-level mindfulness training

The online mindfulness training is composed of seven modules to be completed weekly, over a 7-week time period. Each weekly online module is expected to require participants between 20 to 30 min to complete. Each individual module consists of the following components:A short video introducing the theme for the weekA few paragraphs describing the theme and activities for the weekAn audio-guided meditative stress reduction exerciseSuggestions for brief mindfulness activities that can be performed throughout the dayA brief check-in form for participants to let study staff know how the training is goingA moderated discussion board on which participants can post questions/comments if they wish

The mindfulness training is developed by clinicians and investigators who are trained mindfulness teachers and practitioners. The training is adapted from the widely-used Mindfulness-Based Stress Reduction (MBSR) program, an evidence-based training program originally implemented as in-person training [55, 56]. For our project, the MBSR training content was modified, abbreviated, and revised to accommodate an online format and tailored to meet the constraints and needs of the 9-1-1 TC population.

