### Procedures

#### Implementation protocols

After completing the baseline survey, participants will be assigned a study ID number and are randomized to either start the online mindfulness training (the intervention group) or are assigned to the wait-list control group.

Two weeks following the end of the online mindfulness training all participants will be asked to complete the second survey. Two weeks following the end of the call-center-level toolkit availability, all participants will be asked to complete the third survey.

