#### Online stress reduction toolkit

Following the intervention group participants’ completion of the mindfulness training and completion of the second survey, managers of all participating call centers will be provided with a link to access the Toolkit and are asked to share the link with other administrative personnel at their call center who may be in a position to implement any of the suggested activities. Managers will have access to the Toolkit for 3 months and will receive bi-monthly emails encouraging them to use the Toolkit content and directing them to specific modules of the Toolkit. After 3 months access to the Toolkit, all participants complete the third survey.

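### The participant random intercept imposes one common correlation on surveys about 9, 15 and 24 weeks apart; if correlation decays with the gap, the separate survey-2 standard error is too large and the survey-3 one too small

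*Protocol article*

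**What the plan says.** Under Primary analyses, the protocol article lists the model term by term: fixed effects for group, "time (3 levels; baseline, post intervention and follow up"), site, time-by-treatment and a toolkit term at the third time point, "with a random intercept for participant". No residual structure, random slope or robust standard error is named. The group comparison is stated as follows: "Differences between groups will be assessed using the time-by-treatment interaction term". On error rates: "Hypotheses will be conducted at the 0.05 level of significance without adjustment for multiple comparisons".

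The survey timing comes from other sections:

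- The training runs "over a 7-week time period" (Individual-level mindfulness training).
- "Two weeks following the end of the online mindfulness training all participants will be asked to complete the second survey" (Implementation protocols).
- "Managers will have access to the Toolkit for 3 months" (Online stress reduction toolkit), starting after survey 2.
- "Two weeks following the end of the call-center-level toolkit availability, all participants will be asked to complete the third survey" (Implementation protocols).

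Secondary analyses applies the same model to the MAAS and to the four VAS measures.

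**The concern.** A random intercept with independent, equal-variance residuals makes the correlation between any two surveys the same, however far apart they are. Here the gaps differ by a factor of more than two, the C-SOSI asks about the past week only, and a center-wide intervention falls between surveys 2 and 3. A correlation that weakens over time is a reasonable expectation. Exact equality is the stronger assumption.

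The model pools the three correlations into one and gives the same standard error to the change at survey 2 and the change at survey 3. If the true correlations differ, neither standard error need be right. The survey-2 change matters most, because Sample size and power calculations sizes the trial on a t-test of the pre-post difference. That t-test uses the actual variance of the difference, and the planned model does not. At survey 3 the risk is a test that rejects more often than the stated 0.05.

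**Working it through.** **Inputs from the article.** 65 per group with data, effect size 0.5 on the pre-post difference, 80% power, alpha 0.05 (taken as two-sided), 18% loss, 160 in total.

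**Survey gaps**, taking 3 months as about 13 weeks:

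- surveys 1-2: 7 + 2 = 9 weeks
- surveys 2-3: 13 + 2 = 15 weeks
- surveys 1-3: 9 + 15 = 24 weeks

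**The plan's own figure.** The noncentral t gives power 0.801 at 64 per group and 0.808 at 65. With 18% loss, 130/0.82 = 158.5, so 159 against the stated 160. The sample size reproduces.

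**Formula.** Take complete data, equal variances (SD 1) and n per arm. The random-intercept model estimates the residual variance by the pooled within-person mean square, whose expectation is 1 − m, where m is the mean of the three correlations r12, r23 and r13. Then:

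- model variance of either change contrast = 2(1 − m) × 2/n
- true variance = 2(1 − r12) × 2/n at survey 2, and 2(1 − r13) × 2/n at survey 3
- SE ratio (model/true) = a = sqrt[(1 − m)/(1 − r12)] at survey 2, and b = sqrt[(1 − m)/(1 − r13)] at survey 3
- actual two-sided level = 2Φ(−1.96 × ratio)
- survey-2 power = Φ(0.5 × sqrt(65/2) − 1.96a) = Φ(2.850 − 1.96a)

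**One case in full**, with 0.70/0.65/0.55:

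- m = 1.90/3 = 0.633
- model SE = sqrt(4 × 0.367/65) = 0.150
- true SE = sqrt(4 × 0.30/65) = 0.136 at survey 2 and sqrt(4 × 0.45/65) = 0.166 at survey 3
- ratios 1.11 and 0.90; levels 0.030 and 0.077 (simulation 0.077 to 0.080)
- survey-2 power Φ(2.850 − 2.167) = 0.75

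**Range.** All correlations are assumptions.

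| r12 / r23 / r13 | SE ratio, survey 2 | SE ratio, survey 3 | Level, survey 2 | Level, survey 3 | Power, survey 2 |
|---|---|---|---|---|---|
| 0.70 / 0.70 / 0.70 | 1.00 | 1.00 | 0.050 | 0.050 | 0.81 |
| 0.70 / 0.68 / 0.65 | 1.04 | 0.96 | 0.042 | 0.060 | 0.79 |
| 0.75 / 0.70 / 0.65 | 1.10 | 0.93 | 0.032 | 0.070 | 0.76 |
| 0.70 / 0.65 / 0.55 | 1.11 | 0.90 | 0.030 | 0.077 | 0.75 |
| 0.80 / 0.65 / 0.50 | 1.32 | 0.84 | 0.009 | 0.101 | 0.60 |
| 0.65 / 0.70 / 0.60 | 1.00 | 0.94 | 0.050 | 0.067 | 0.81 |
| 0.70 / 0.78 / 0.65 | 0.98 | 0.91 | 0.054 | 0.074 | 0.82 |

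Under pure exponential decay over 9, 15 and 24 weeks, with a 9-week correlation from 0.50 to 0.90, the survey-2 level is 0.023 to 0.011, the survey-3 level 0.079 to 0.104, and survey-2 power 0.72 to 0.62.

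**Simulation.** Runs of 20,000 or more trials, complete data, 65 per arm, agree with the formulas. With a 9-week correlation of 0.75 and exponential decay, the levels are 0.015 and 0.097. Setting the follow-up SD to 0.85 or 1.2 times the baseline SD leaves both directions unchanged. The joint two-degree-of-freedom interaction test rejects in 0.053 to 0.059 of null trials under exponential decay, and in 0.051 to 0.058 for the 0.70/0.68/0.65, 0.70/0.65/0.55 and 0.80/0.65/0.50 patterns. If each contrast instead uses its own change variance, as an unstructured covariance does with complete data, the levels are 0.048 to 0.051 for those three patterns and for 0.70/0.78/0.65.

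**The case against.** - **The stated test may be the joint one.** Time has three levels, so the interaction read literally is a single test on two degrees of freedom, and that test is little affected. This stands. A reader might infer that the primary test as a whole is invalid, and the documents do not support that. The article does not fix the joint test as the decision rule, however. It also refers to interaction terms in the plural, and it sizes the trial on the pre-post difference, so a separate survey-2 reading is natural.
- **No correlations are given.** A reader might infer that both standard errors are certainly wrong. They are wrong only if the correlations differ. The survey-2 direction needs r12 to exceed the average of the other two. Uneven response to training between surveys 1 and 2 could lower r12, and the last two rows of the table then show no error or a slight reversal at survey 2. The survey-3 direction is more robust.
- **Residual structure and robust standard errors may sit in a fuller plan.** That is possible, and the figures hold only without them. But the article does state a within-person term, so the point concerns what is written as well as what is left out.
- **Dropout.** A reader might add that the wrong covariance biases the estimates under dropout. None of the checks used incomplete data, and the article plans not-missing-at-random sensitivity analyses, so that claim is not made here.

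**Conclusion.** The concern holds in conditional form. As written, the model imposes equal variances and one correlation on three unequally spaced surveys. If correlation decays steadily with the gap, r12 lies above the mean correlation and r13 below it, so the survey-2 standard error is too large and the survey-3 standard error too small.

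The size runs from trivial to moderate across the decay patterns examined: a survey-2 level of about 0.042 down to 0.009, a survey-3 level of about 0.06 up to 0.10, and a loss of about 2 to 21 points of power on the contrast for which the trial was sized. It is zero with equal correlations.

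This rests on assumed correlations, independent residuals, model-based standard errors and complete data at 65 per arm. It concerns the separate contrasts, not the joint interaction test. The change is worth making because it is cheap and removes an assumption that the trial does not need.

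**What to change.** In the primary model, replace the participant random intercept by an unstructured 3x3 within-participant covariance, with Kenward-Roger degrees of freedom. Prespecify a fallback for non-convergence: heterogeneous Toeplitz, or the random intercept with robust standard errors. Use the same structure for the MAAS and the four VAS models.

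The cost is four extra covariance parameters (six against two), with up to 160 × 3 = 480 observations, and a small convergence risk that the fallback covers. No new data are needed.
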